#### Eligibility Criteria

The inclusion criteria entail participants aged 18 to 30 years old and an individual who scores more than 4 or higher levels of ACE. This age group spans the young adulthood phase of an individual, and it is considered a significant developmental stage characterized by exposure to unique challenges and opportunities [21]. Meanwhile, the exclusion criteria are individuals receiving any type of intervention, demonstrating any severe psychopathology or psychiatric illness that requires a psychopharmacological approach, and those who had received intervention or therapy consistently in the past. Individuals need to fulfil the criteria to be recruited as mentioned above. Individuals will be recruited through multiple centers and social media platforms

#### Participant Recruitment and Randomization

The participants for this study are Malaysian youths with ACE, particularly those visiting the Psychological Department at the National University of Malaysia Medical Centre. During the selection stage, participants will be approached by the researcher and seek their consent to participate in the study. Those providing affirmative responses will then be instructed to fill up the self-administered ACE questionnaire.

This assessment period is the screening stage to identify those that fulfil the inclusion criteria. Participants who score four or more of ACE will then be included in a pool of participants and assigned randomly to either the control group or intervention group. Random assignment procedure will be implemented by random allocation software, Research Randomiser [31], to generate numbers and assign participants to an intervention group or control group. Allocation concealment will be performed by a single blinding procedure, whereby the assessors of the outcome measures will be unaware of the specific group the participants belong to. In other words, only the investigator allocating participants to either the control or intervention group will be aware of this information while other assessors are blinded. Table 1 depicts the participant enrolment schedule, time points and assessments to be performed during the study period.

**Table 1 table1:** SPIRIT (Standard Protocol Items: Recommendations for Interventional Trials) schedule of enrolment, interventions, and assessments.

			Study period							Close-up
			Enrolment		Allocation		Postintervention		Four-week follow-up	
Timepoint			t_1_		0		t_2_		t3+4weeks	
**Enrolment**			✓							
	Screening	✓								
	Eligibility screen	✓								
	Informed consent	✓								
	Allocation			✓						
**Interventions**										
	Intervention A									
	Control									
**Assessments**										
	Brief Coping Orientation to Problem Experienced Scale - English and Malay version	✓				✓		✓		
	Ryff’s Scale of Psychological Well-being (SPWB) - English and Malay version	✓				✓		✓		
	Quality of Life –WHOQL-BREF - English and Malay Version	✓				✓		✓		
	Subjective stress – Perceived Stress scale - English & Malay version	✓				✓		✓		
	Personal Resources Questionnaire 2000 - English and Malay version	✓				✓		✓		
	Adult Resilience Measure-Revised - English and Malay version	✓				✓		✓		
	Biomarker - measure changes in salivary cortisol	✓				✓				
	Blood pressure (blood pressure measured with a sphygmomanometer	✓				✓				

Participants in the control group will receive no intervention, while those in the intervention group will receive five sessions of resilience-building intervention conducted by a trained facilitator. Hotlines, post session, and appropriate resources will be provided for those reporting distress after the intervention. Investigators will be blinded throughout the whole process of randomization and data collection as the whole process is handled by a research assistant (randomization), counsellor, and clinical psychologist (data collection). Under no circumstances will unbundling occur as a research assistant, counsellor, and clinical psychologist are briefed with the standard operating procedure to follow when an incident occurs. The flow diagram is presented in Figure 1.

**Figure 1 figure1:**
[figure not shown]
Consolidated Standards of Reporting Trails 2010 flow diagram.

#### Contents and Delivery Method of the Intervention

The intervention will be adapted and modified according to the R2 Resilience building program designed by Ungar [20], which comprises 7 principles; help people to navigate, help people to negotiate, think about systems, coordinate services and supports, provide continuous support, be relevant to place and culture, and share responsibility for solutions. These principles will guide the process of modifying the intervention and the principles will be reflected in each session. The intervention will be delivered in 5 sessions.

Session 1 is divided into subsessions entitled “Self-exploration” and “Social support.” The first subsession focuses mainly on building rapport with the participants and helping them explore their coping skills, strengths, weaknesses, and talents. The second subsession emphasizes the importance of social support to enhance a sense of belonging and connection, as well as explore resources relating to social support. Both sessions will be delivered via internet-based with each lasting for 60 minutes.

The second session is also divided into 2 parts, coping technique including cognitive flexibility and grounding technique, and coping skills. The coping technique focuses on participants’ coping strategies and a deeper insight compared with the first session. This section also aims to provide cognitive exercise for preventing catastrophic thinking. As for coping skills, the strategies will be discussed in depth and practiced together with the facilitators. Participants will also be directed to work in pairs and assisted to identify their best coping strategies, either emotion-focused or solution-focused.

The third session comprises 2 parts to familiarize the participant with resource findings and explore their understanding of resilience. First, the facilitator will recap what the participant has learnt in the previous sessions and help identify where they can get help and access the available resources. Such assistance will be tailored for each participant to learn about resilience resources and harnessing them accordingly. In the second part, in-depth discussion will be held with each participant by focusing on past ACEs and how they were able to overcome the experiences, as well as their past resilience resources. Both sessions will be delivered via internet-based with each lasting for 60 minutes.

The fourth session is also divided into 2 subsessions; (1) what is resilience to you (part II), and (2) spirituality. The first subsession is the continuation of the second part of the third session with the same components as shown in Table 2. Meanwhile, the second subsession entails learning from each other regarding the role of religion and spirituality in addressing past adversities. The last session is the “Resilience-building (wrap-up),” whereby all the intervention components will be reviewed and visualized in the form of a diagram. Each session of the intervention will last for 2 hours (60 minutes for each session, with 15-minute breaks between sessions). Each session will be conducted weekly, week 1 for the first session and week 5 for the fifth session respectively. All sessions of the intervention will be administered via internet-based to each participant by the facilitators.

**Table 2 table2:** Components of the intervention.

Week	Session	Session	Duration	Mode of delivery	Focus
Week 1	1st session (1A)	Session 1A: Self-exploration	60 minutes	Internet-based	Build rapport among students with an ice-breaking activity To help participants explore their coping skills, strengths, weaknesses, and talents
Week 1	1st session (1B)	Session 1B: social support	60 minutes	Internet-based	To talk about the importance of social support To foster a sense of belonging and connection. To explore resources regarding social support
Week 2	2nd session (2A)	Session 2A: coping techniques: cognitive flexibility and grounding technique	60 minutes	Internet-based	Explore participants’ coping strategies (be mindful of labelling participants’ strategies). Go deeper from session 1A Cognitive exercise to prevent catastrophic thinking How do you practice cognitive exercise? What is fallacy thinking? Introduce A-B-C and how to practice them
Week 2	2nd session (2B)	Session 2B: coping skills	60 minutes	Internet-based	Discuss the strategies in depth and practice them together. (Follow up from Session 2A) Finding allies (participants form a pair and check in with each other) Emotion-focused coping vs. solution-focused coping During a crisis, how do these routines help? Helping the body to feel safe
Week 3	3rd session (3A)	Session 3A: resource finding	60 minutes	Internet-based	Review and monitor from the previous session to recap what has been learned To help participants know where to get help and the resources available To help participants learn about their resilience resources and how to tap into them
Week 3	3rd session (3B)	Session 3B: what is resilience to you?	60 minutes	Internet-based	How do you survive? What is the meaning of your stories? What are your resilience resources in the past?
Week 4	4th session (4A)	Session 4A: what is resilience to you? part II	60 minutes	Internet-based	How do you survive? What is the meaning of your stories? What are your resilience resources in the past?
Week 4	4th session (4B)	Session 4B: spirituality	60 minutes	Internet-based	Review and monitor from the previous session to recap what has been learned To learn from each other about the role of religion and spirituality
Week 5	5th session (5A)	Session 5B: eesilience-building (wrap-up)	120 minutes	Internet-based	To review and discuss all of the components To draw a diagram with all of the components involved

#### Intervention Protocol and Fidelity

The intervention will be conducted in Malay or English. It aims to encompass both languages and will be provided according to the participant’s native language. Therapists will be trained to follow the protocol and the manual. A recap will be conducted at the end of the session. Dynamic assessment will be used to track the learning progress. Participants will use journaling as a method to practice their skills. In addition, progress and practice will be discussed at the beginning of each session. As for intervention fidelity, journals and progress of group sessions will be collected from mental health professionals after each session to ensure they continue a similar structure for the intervention. The checklist will be prepared for the mental health professional.

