#### Sample Size

Sample size calculation was performed using G*power 3.1 software (Heinrich-Heine-Universität Düsseldorf). By assuming a study power of 0.8, 95% CI (α=0.05), and a moderate effect size of 0.25 as recommended by Ferguson (2009), the *F*-test was selected alongside repeated measures ANOVA with in-between interaction, with 2 groups and the number of measurements. Thus, a total sample size of 36 was obtained, reflecting 18 participants per group. We considered a high drop-out rate of 50% as several individuals may be unwilling to participate given the adverse effects of ACEs and confidentiality in sharing experiences with the researchers. Therefore, the sample size was increased to 50, amounting to 25 participants per group.

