### Data Analysis

All data management and statistical analysis will be conducted using SPSS (version 26; IBM Corp). Data management will be performed by screening for missing data and checking for potential outliers. Descriptive statistics will be used to assess the data normality and to summarize the pre and postintervention scores for each group at different periods. Mean and SDs will be provided for normally distributed data, followed by mixed ANOVA with repeated measures to compare the pre and postintervention mean scores between and within the groups.

The assumptions of ANOVA include randomly collected and normally distributed data, sufficient sample size, homogeneity of variances, and absence of violation and outliers. Levene’s test will be applied to test the homogeneity of variance. Mixed ANOVA benefits RCT design as it allows testing for 2 groups across 2-time points. Mixed ANOVA analysis aims to handle response outcomes conducted on the same experimental unit at a different time or under different conditions [57]. The differential effects of the intervention components will be tested with interactions between the component and time. These analyses will model random slopes and intercepts for participants, explore the fixed effects of the condition, and test the repeated measures over time. This type of analysis is advantageous by accounting for missing values through the maximum likelihood estimation method [57]. Effect sizes will be computed based on Cohen *d*.

In addition, the intention-to-treat analysis will be applied to analyze the participants according to their assigned groups. This analysis includes all participants and ignores noncompliance, protocol deviation, and withdrawal. The intention-to-treat analysis is a complete trial strategy for the design, execution, and analysis of RCT, focusing on the consolidated standard of reporting trial guidelines. Thus, the number of participants in each assigned group will be analyzed by the intention-to-treat principle.

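### Whether sessions are run in groups or individually is contradictory; if in groups, the stated model and sample size ignore clustering in the intervention arm

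*Protocol article*

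**What the plan says.** **Wording that points to groups.** Intervention Protocol and Fidelity says that "journals and progress of group sessions will be collected from mental health professionals after each session", and Data Auditing and Management repeats this. Table 2 opens with an ice-breaking activity, and session 2B includes "Finding allies (participants form a pair and check in with each other". The text on session 2 also has participants working in pairs, and session 4 involves "learning from each other regarding the role of religion and spirituality". The Discussion mentions counselling after the group for anyone distressed.

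**Wording that points to individuals.** Contents and Delivery Method of the Intervention states that "All sessions of the intervention will be administered via internet-based to each participant by the facilitators". The same section describes session 3 as assistance tailored to each participant, followed by an in-depth discussion with each participant, which session 4A continues.

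**Control arm.** It receives no intervention (Study Design and Setting).

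**Analysis.** Data Analysis says that "Mixed ANOVA analysis aims to handle response outcomes conducted on the same experimental unit at a different time". It then specifies random slopes and intercepts for participants and a fixed effect of condition. It names no term for session group, pair or facilitator.

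**Sample size.** The inputs are "a study power of 0.8, 95% CI (α=0.05), and a moderate effect size of 0.25" for "repeated measures ANOVA with in-between interaction, with 2 groups and the number of measurements". The result is 36 in total, raised to 50 (25 per arm) for dropout. No ICC or design effect appears.

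**The concern.** People who meet in the same online group for five weekly sessions share a facilitator, peers and a discussion. Their outcomes would usually be expected to be more alike than those of unrelated people. Untreated controls have no such link, so the design would be partially nested: clustered in one arm and independent in the other.

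Participant-level random effects deal with repeated measurements on one person. They do nothing about correlation between members of the same session group. If that correlation is positive, the standard error of the arm-by-time effect is too small, and the type I error exceeds 5% for every outcome analysed this way. The sample size would be optimistic for the same reason.

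**Working it through.** **Step 1: the plan's own figure.** For the within-between interaction, λ = f²·N·m/(1−ρ), with df1 = (k−1)(m−1) and df2 = (N−k)(m−1). From the article: f = 0.25, α = 0.05, k = 2. The Sample Size section gives neither the number of measurements m nor the correlation ρ. I take m = 2 from Data Analysis ("Mixed ANOVA benefits RCT design as it allows testing for 2 groups across 2-time points") and assume ρ = 0.5.
- N = 34 gives power 0.807.
- N = 36 gives power 0.830.

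The stated 36 is therefore matched to within 2 participants, as a calculation in which everyone is independent. With m = 3 and ρ = 0.5, N = 28 would suffice (power 0.812), which does not match.

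**Step 2: effect of clustering in one arm.** Group size g and ICC are not in the article, so both are assumed. The relevant ICC is that of the quantity tested, the change score.
- Intervention-arm design effect: DE = 1 + (g−1)·ICC. Control arm: 1.
- True/naive standard error ratio: R = √((1+DE)/2).
- The naive standard error is too small by 1 − 1/R.
- True type I error: P(|t₄₈| > 2.011/R), with 25 per arm.

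| g | ICC | DE | R | Naive SE too small by | True α |
|---|---|---|---|---|---|
| 2 | 0.05 | 1.05 | 1.012 | 1.2% | 0.053 |
| 2 | 0.20 | 1.20 | 1.049 | 4.7% | 0.061 |
| 5 | 0.01 | 1.04 | 1.010 | 1.0% | 0.052 |
| 5 | 0.05 | 1.20 | 1.049 | 4.7% | 0.061 |
| 5 | 0.10 | 1.40 | 1.095 | 8.7% | 0.073 |
| 8 | 0.05 | 1.35 | 1.084 | 7.7% | 0.070 |
| 8 | 0.10 | 1.70 | 1.162 | 13.9% | 0.090 |
| 12 | 0.05 | 1.55 | 1.129 | 11.4% | 0.081 |
| 12 | 0.10 | 2.10 | 1.245 | 19.7% | 0.113 |

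Simulation (40,000 runs per cell) agrees: 0.061 for groups of 5 at ICC 0.05, and 0.117 for two groups of 12 at ICC 0.10 (24 per arm).

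**Step 3: effect on sample size.** Multiplying 36 by (1+DE)/2 gives 39.6 for g = 5 at ICC 0.05 and 55.8 for g = 12 at ICC 0.10. This is before dropout and before any loss of degrees of freedom. At 18 per arm, approximate power under a valid test falls from 0.83 to 0.79 and 0.65 respectively.

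**Step 4: which model term corrects it.** Take 25 per arm, intervention groups of 5, unit outcome variance and ρ = 0.5, so that the change score has variance 1. By generalised least squares, the standard error of the arm-by-time effect is:
- no group term: √(1/25 + 1/25) = 0.283;
- a session-group intercept that is constant over time: 0.283, because it cancels from the pre-post contrast;
- a session-group effect with variance 0.1 acting after baseline only: √(1/25 + 0.1/5 + 1/25) = 0.316.

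Only the last form changes the test.

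**Step 5: cost in interval width.** I use Satterthwaite degrees of freedom, with the number of groups minus one for the intervention arm. Widening is R times the ratio of t quantiles.
- 5 groups of 5, ICC 0.05: df about 12; 1.049 × 2.178/2.011 = 1.14.
- 3 groups of 8, ICC 0.05: df about 6; 1.084 × 2.469/2.013 = 1.33.
- 2 groups of 12, ICC 0.10: df about 2; 1.245 × 4.015/2.013 = 2.48.

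**The case against.** A reader might infer that the standard errors and p values simply are too small. The article does not support that. The inflation needs group delivery and a positive ICC, and neither ICC nor group size is given. The only grouping with a stated size is the pair, and for pairs the inflation is slight. Several phrases, not just one, describe delivery to individuals. The firm fact is a contradiction about format, and the inferential error depends on how it is resolved. This objection stands, and it makes the point conditional.

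It can also be said that a condensed article may leave facilitator and group terms to a fuller analysis plan. This carries less weight, because Data Analysis does state its random effects, and they are for participants only. Nor does the wording about individuals remove the issue. Pair work and learning from one another cannot happen in purely one-to-one sessions, and shared facilitators could still induce correlation.

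Finally, with 25 in the intervention arm, groups of 5 to 12 mean only about 5 down to 2 clusters. Where the potential harm is largest, the ICC is hardest to estimate. That also stands, and it shapes the remedy.

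**Conclusion.** The point holds in conditional form. The article contradicts itself on delivery format. If sessions are run in groups, the stated model and the sample size both ignore clustering that would arise in the intervention arm only.

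Given a positive ICC, and assuming groups of 5 to 12 with ICC 0.05 to 0.10, the naive standard error is about 5 to 20% too small and the nominal 5% test runs at about 6 to 11%. If only pairs cluster, with ICC 0.05 to 0.20, it runs at about 5.3 to 6.1%. With groups of 5 and ICC 0.01, the effect is negligible (5.2%). The matter should be settled before the final analysis, but its size cannot be fixed from the document.

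**What to change.** 1. State the delivery format for each session and reconcile the group and individual descriptions. If delivery is in groups, give the group size and the number of groups and facilitators.
2. Record session-group and facilitator identifiers. Session records are already collected after every session, so these may be recoverable for participants already treated.
3. If delivery is in groups, add to the primary model a session-group effect in the intervention arm only, with each control as its own cluster. It must act after baseline: either a group-by-time random effect, or a baseline-adjusted post-score model with a session-group random effect. A time-constant group intercept is not enough.
4. Use small-sample degrees of freedom (Satterthwaite or Kenward-Roger) and report the ICC.
5. Because the ICC will be poorly estimated from few groups, show the clustered analysis alongside results over a range of assumed ICCs.

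**Cost.** Two identifier fields, one model term and wider confidence intervals: about 14% wider with five groups at ICC 0.05, about 33% with three groups of 8 at ICC 0.05, and about 150% with two groups of 12 at ICC 0.10. Results reports only 14 participants in the intervention arm by January 2025, with two withdrawn, so there may be few groups. If sessions prove to be individual, a clear statement resolves the contradiction, and the session-group term is not needed.

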### Data Collection Instruments and Outcome Measures

#### Adverse Childhood Experience Questionnaire

The Adverse Childhood Experience Questionnaire (ACE-Q) is a 10-item measure to assess events of traumatic or adverse experiences that an individual experienced before the age of 18 years. The instrument evaluates the individual’s exposure to childhood physical, psychological, or sexual abuse, as well as household dysfunction such as substance use, domestic violence, and incarceration. The ACE-10 has been validated among the Malaysian population with an acceptable internal consistency of 0.86 and internal validity ranging from 0.28-0.70 [49].

#### Patient Health Questionnaire-9

The English and Malay versions of the Patient Health Questionnaire-9 (PHQ-9) will be used in this study to assess depression among youths with ACEs. The instrument has been validated among the Malaysian population by Sherina et al [50] with a sensitivity of 87% (95% CI 71%-95%) and specificity of 82% (95% CI 74%-88%). It was also reportedly suitable as a case-finding instrument in Malaysian primary care clinics.

#### Brief Coping Orientation to Problem Experienced Scale

The brief coping orientation to problems experienced (COPE) instrument comprises 28 items with 14 broad coping strategies. The Malay version of the instrument was validated by Saiful [51] among secondary school adolescents and was found to be valid and reliable in identifying coping strategies. Specifically, the overall Cronbach α value was 0.83 with the majority of the coping strategies reflecting acceptable internal consistency.

